## Other study parameters

The continuous variables will be presented as quantitative variables. The ANCOVA will be used to adjust for baseline values. The X^2^ test will be used for nominal variables. A P-value of less than 0.05 was considered statistically significant. Patients were analysed based on per protocol principles.

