# OBJECTIVES

**Objective:** What are the 6-week and 12-week effects on the functional outcome scores of the ankle in early weight bearing (mobilization with Walker) compared to 6 weeks non-weight bearing and immobilization in conservatively treated stable ankle fractures (Weber B or Lauge Hansen supination-eversion stage 2-4A)?

**Secondary Objective:** What is the 6-week effect on dislocation of the fracture in early weight bearing (mobilization with Walker) compared to 6 weeks non-weight bearing and immobilization in conservatively treated stable ankle fractures (Weber B or Lauge Hansen supination-eversion stage 2-4A)?

**Other Objectives:** Other outcome measures include range of motion (ROM) of the ankle circumference of the calf, return to work, mental health outcome scores and rates of other complications.

**Hypothesis 1:** We expect earlier functional outcomes in the intervention group than in the control group.

**Hypothesis 2:** We expect the number of complications not to be higher in the intervention group than in the control group.

**Hypothesis 3:** We expect the long-term recovery function (3 months) in the intervention group not to be worse than in the control group.

**Null hypothesis 1**: The treatment in the intervention group is not as effective as the treatment in the control group, because there are worse functional outcomes in the intervention group than in the control group.

**Null hypothesis 2:** The treatment in the intervention group is not as safe as the treatment in the control group, because there are more dislocations of the fractures reported in the intervention group than in the control group.

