**Follow-up**

The patients will visit the traumatology department after 6 weeks ***(= t2)*** and 12 weeks ***(= t3)*** posttraumatic. During the visit after 6 weeks, radiographs of the ankle joint are obtained at 3 different views (anteroposterior (AP), lateral and Mortise). Furthermore, they will undergo a comprehensive examination that will include assessment of ankle dorsal flexion/ plantar flexion with use of a goniometer. The circumference of the calf will be measured with a tapeline. This will be performed by the trained research staff or by doctors trained and instructed by them.

Each visit ***(t1, t2 ánd t3)*** the patients receive 2 questionnaires with regard to return to work or sport, daily activities and limiting factors.

[figure not shown]

Figure 1. Flowchart

[figure not shown]

Figure 2. Timeline

| Variable (outcome measure) | Type | t1 | t2 | t3 | Total |
| --- | --- | --- | --- | --- | --- |
| Functional outcome score (OMAS, 0-100) | continuous | ✓ | ✓ | ✓ | 3 |
| Dislocation of the fracture (Yes/No) | binary | ✓ | ✓ | × | 2 |
| Range of motion of the ankle (degrees) | continuous | ✓ | ✓ | ✓ | 3 |
| Circumference of the calf (cm) | continuous | ✓ | ✓ | ✓ | 3 |
| Return to work (%) | continuous | ✓ | ✓ | ✓ | 3 |
| Satisfaction (SF-36, 0-100) | continuous | ✓ | ✓ | ✓ | 3 |
| Other complications | nominal | × | ✓ | ✓ | 2 |

Table 1. Measurements

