### Other study parameters

Range of motion (ROM) of the ankle and circumference of the calf (physical examination), return to work, mental health outcome scores (SF-36 questionnaire) and other complications, such as deep vein thrombosis or surgery.

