## Secondary study parameter(s)

The categorical data will be presented as qualitative variables. Starting with a univariate analysis, the X^2^ test will be used for the binary variables. A risk ratio, including 95% confidence intervals, will be used to indicate the probability of a dislocation of the fracture in comparison to both groups. Thereafter, we will use a multivariate logistic regression analysis, at which the odds ratio will adjust for baseline values. A P-value of less than 0.05 was considered statistically significant. Patients were analyzed based on per protocol principles.

If there is a suspicion of a dislocation of the fracture, based on the assessment of the radiograph and low functional outcome scores, a Computed Tomography (CT) of the ankle will be made to confirm this. Thus, we want the type I error to be controlled.

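### Other complications are set up as one nominal variable with a chi-squared test, a weak and non-directional way to judge whether more Walker patients have a complication

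*Protocol*

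**What the plan says.** Hypothesis 2 (Protocol, section 2) is directional and concerns a number: "We expect the number of complications not to be higher in the intervention group than in the control group". Null hypothesis 2 narrows the safety question to dislocation: the treatment is less safe "because there are more dislocations of the fractures reported in the intervention group than in the control group".

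The analysis sections treat the two kinds of complication differently.

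- **Dislocation.** Table 1 types it as binary. Section 10.2 says that the chi-squared "test will be used for the binary variables", and adds an effect measure: "A risk ratio, including 95% confidence intervals, will be used to indicate the probability of a dislocation of the fracture". An adjusted logistic regression follows.
- **Everything else.** Section 8.1.3 describes these as "other complications, such as deep vein thrombosis or surgery". Table 1 gives them one row, "Other complications | nominal", recorded at t2 and t3. Section 10.3 says that the chi-squared "test will be used for nominal variables", with the criterion "A P-value of less than 0.05 was considered statistically significant". It plans no risk ratio, risk difference, interval or count of affected patients.

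'Other complications' is the only nominal row in Table 1, so the sentence on nominal variables in section 10.3 must be meant for it. Section 10.4 reuses the methods of section 10.3 at the interim analysis.

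**The concern.** A chi-squared test of arm by complication type has as its null that the distribution over categories is the same in both arms. Hypothesis 2 asks whether more patients are affected in one arm. The two questions differ in three ways.

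1. The test has no direction. A small p-value does not say which arm is worse.
2. Each extra type costs a degree of freedom, so a general excess in one arm is diluted.
3. A different mix of types can produce a significant result when equal numbers of patients are affected. The protocol gives some reason to expect different mixes: section 1 links plaster immobilisation to thrombosis, and section 11.4 names myalgia as a risk of the investigational treatment.

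Section 11.4 also expects dislocation to be rare. The other complications may therefore supply most of the events that bear on Hypothesis 2, and they are the part with no planned estimate or interval.

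**Working it through.** **Inputs.** The protocol gives no rate for other complications, no list of types and no margin, so it has no figure of its own to reproduce here. Section 4.4 gives a total of 50; 25 per arm assumes equal allocation. (The same sentence also gives 46 per group, which does not fit a total of 50; the total is used here.) Alpha is 0.05. All rates, numbers of types and mixes below are assumptions.

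**Step 1: hand examples.** Pearson X² = Σ(O − E)²/E, without correction. With equal arms, E is half of each column total.

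*An excess with the same mix, 'none' counted as a level.* Walker 13/6/4/2 and control 19/3/2/1 (none and three types). E = 16, 4.5, 3, 1.5.
X² = 2(3²/16) + 2(1.5²/4.5) + 2(1²/3) + 2(0.5²/1.5) = 1.125 + 1.000 + 0.667 + 0.333 = 3.125 on 3 df, p = 0.37.
The same patients as any complication, 12/25 v 6/25: X² = 2(3²/16) + 2(3²/9) = 3.125 on 1 df, p = 0.077. The statistic is identical; only the degrees of freedom differ. The smallest expected count in the nominal table is 1.5, so the chi-squared approximation is also weak there.

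*The same excess, types among events only.* 6/4/2 v 3/2/1: every O equals its E, so X² = 0 and p = 1.00. A doubling leaves no trace.

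*Equal numbers, different types.* 8/25 affected in each arm, all of one type in one arm and all of another in the other: X² = 0 + 2(4²/4) + 2(4²/4) = 16.0 on 2 df, p = 0.0003, although neither arm has more complications.

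*What an interval adds.* For 12/25 v 6/25 the risk difference is 0.48 − 0.24 = 0.24. SE = √(0.48·0.52/25 + 0.24·0.76/25) = √0.01728 = 0.131, so the 95% interval is 0.24 ± 1.96·0.131, or about −0.02 to 0.50. A reader learns the direction and how large an excess remains possible; the nominal p of 0.37 gives neither.

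**Step 2: power against a true excess.** Simulation with 100,000 runs, 25 per arm, 10% v 40% of patients affected, same mix in both arms, 'none' included as a level, empty columns dropped.

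| Number of types | Nominal X² | 2×2 uncorrected X² | 2×2 Fisher exact |
|---|---|---|---|
| 2 | 59% | 73% | 59% |
| 3 | 49% | 73% | 59% |
| 4 | 41% | 73% | 59% |
| 6 | 27% | 73% | 59% |

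Against the uncorrected 2×2 test the loss is 14, 24, 32 and 46 points. Against Fisher's test it is 0, 10, 18 and 32 points.

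**Step 3: rejection when equal numbers are affected.** Two types, same total rate in both arms, mix reversed between arms.

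| Affected in each arm | Nominal X², 80/20 v 20/80 | Nominal X², 65/35 v 35/65 | 2×2 uncorrected X² |
|---|---|---|---|
| 10% | 11% | about 3.5% | about 5% |
| 20% | about 34% | about 10% | about 5% |
| 30% | 55% | 15% | about 5% |

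Under the 80/20 reversal with only 4% and 8% affected, the nominal test rejects in about 1% and 6%.

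**The case against.** **Hypothesis 2 is not left to this test alone.** A reader might infer that the whole hypothesis is judged by a test of another question. The documents do not support that. Null hypothesis 2 states the safety question as dislocation, which is the secondary endpoint and has a two-by-two test, a risk ratio with interval and a logistic regression. The point concerns only the other complications, a lower-tier parameter.

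**The test is not necessarily blind to number.** It would be so only if the levels were types among events. If 'none' is a level, as in the simulation, the test does respond to number, though weakly and without direction. The protocol does not list the levels.

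**The single multi-category table is an inference.** A yes/no item for each complication is also nominal. Section 10.3 uses the plural, and section 2 speaks of rates. Separate two-by-two tests for thrombosis and for surgery would have no mix problem and could hold a patient with two events. Coding detail may also sit in an analysis plan that is not shown. This stands in part: one cannot assert that the planned coding fails for patients with several complications. But Table 1 sets one row, typed differently from the yes/no dislocation row, and on either reading section 10.3 plans neither a count of affected patients nor an interval.

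**The size depends on the comparator and the assumed mix.** The 24 to 46 point loss with 3 to 6 types holds only against the uncorrected 2×2 test. Against Fisher's test there is no loss with two types, the number that section 8.1.3 names as examples. The high false-signal rates need a strong reversal of mix, and both arms receive thromboprophylaxis (section 3), which weakens the case for a large difference in thrombosis. These points stand.

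**Conclusion.** The point holds for the other-complications part of Hypothesis 2. The planned nominal chi-squared is a poor test of whether more Walker patients have a complication, and no effect size or interval accompanies it.

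The loss of power runs from nothing (two types, Fisher's test as comparator) to 46 points (six types, uncorrected 2×2 test as comparator). The false-signal rate at equal totals runs from about 3% to 55% over the mixes and the 10% to 30% rates tried. These figures rest on 25 per arm, on assumed rates and mixes, and on 'none' being a level.

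The missing direction and the missing estimate do not depend on those assumptions. They matter more than any single power figure, because Hypothesis 2 claims that something is not higher. A non-significant result from any of these tests would not show that, and the protocol states no margin. This is a change worth making to a lower-tier analysis; it does not undermine the primary analysis or the dislocation analysis.

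**What to change.** In Table 1 and section 10.3:

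- Define a per-patient binary variable: at least one other complication up to t3, yes or no.
- Compare the arms as a two-by-two table and report a risk difference or risk ratio with its 95% confidence interval, following the approach already planned for dislocation. The risk difference stays defined if one arm has no events.
- List complications by type and arm descriptively, without a test.
- State that the interval is the evidence on whether the number is higher, and that a non-significant result will not be read as showing that it is not. If the sponsor wants a formal conclusion, a margin has to be stated and justified first.

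The cost is a change of wording. The information is already collected at t2 and t3, and the interim analysis in section 10.4 would take over the change without further edits. There is one small downside: a difference confined to a single type would be described and not tested.

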## Interim analysis (if applicable)

At the end of April 2018 an interim analysis will be done by the investigator. The same statistical methods will be used as described in Chapter 10.1, 10.2 and 10.3. The advice(s) of the DSMB will be taken into account and implemented if necessary.

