## Data Safety Monitoring Board (DSMB)

The Clinical Trial Center Maastricht (CTCM) will be monitoring the study for its safety. It’s an independent committee and it has no conflict of interest with the sponsor of the study . The advice(s) of the DSMB will only be sent to the sponsor of the study. Should the sponsor decide not to fully implement the advice of the DSMB, the sponsor will send the advice to the reviewing METC, including a note to substantiate why (part of) the advice of the DSMB will not be followed.

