## Primary study parameter(s)

The continuous variables will be presented as quantitative variables. The ANCOVA will be used to adjust for baseline values. A P-value of less than 0.05 was considered statistically significant. Patients were analysed based on per protocol principles.

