## Public disclosure and publication policy

We will publish the results with a national and international article. If the inclusion is not achieved within the stipulated time, we will make a report of the preliminary results. We hope to be able to present the results of this research at regional or national level.

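### Section 10.4 schedules an investigator-run comparative interim analysis at the same unadjusted p < 0.05 as the final analysis, with no stated purpose or decision rule

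*Protocol*

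**What the plan says.** Section 10.4 fixes the date and the operator: "At the end of April 2018 an interim analysis will be done by the investigator". It fixes the methods by reference: "The same statistical methods will be used as described in Chapter 10.1, 10.2 and 10.3". It then adds: "The advice(s) of the DSMB will be taken into account and implemented if necessary".

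Each of the three sections referred to carries its own threshold. Section 10.1, on the primary outcome (OMAS), says: "The ANCOVA will be used to adjust for baseline values. A P-value of less than 0.05 was considered statistically significant". Section 10.2, on dislocation, uses the same 0.05. Section 10.3 says: "The X^2^ test will be used for nominal variables. A P-value of less than 0.05 was considered statistically significant". None gives a different threshold for the interim or the final look.

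Section 9.5 names a monitoring body for safety and calls it an "independent committee and it has no conflict of interest with the sponsor" of the study, but does not give it the interim analysis. Section 8.2 states that neither patients nor researchers can be blinded. Section 11.2 has the investigator check weekly whether patients were told about the study, and telephone and e-mail those who were not.

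**The concern.** A comparative interim look needs a purpose, a rule for what follows from it, and a threshold that takes account of the second test. Section 10.4 supplies none of these and does specify something else: the final-analysis tests, at the final-analysis threshold, run early by the investigator.

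Two things are at stake. The first is the false-positive rate of the primary comparison: two chances to cross 0.05 give more than 5% if either crossing can count. The second is operational. Someone in contact with recruitment would know which arm is ahead while patients may still be entering and being followed. That knowledge can influence how the trial is presented to patients not yet enrolled.

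**Working it through.** **What the protocol gives.** Alpha is 0.05 in Sections 10.1, 10.2 and 10.3, and the same methods apply at the interim (Section 10.4). The interim is set by calendar date only, with no patient number or information fraction. Section 4.4 sizes the trial at 23 per group for 80% power at 0.05 and does not mention the interim.

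**What has to be assumed.** The test is two-sided, since the protocol does not say. The information fraction at the interim, *t*, is unknown and is varied. One endpoint is considered at a time.

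**The plan's own figure.** The nominal error is 5%. Simulated t-tests under no difference (100,000 runs), judged at the final look only, rejected in 4.99% of runs with 23 per group and 4.89% with 25 per group. A single final test therefore reproduces the plan's 5%.

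**Two looks, success possible at either.** Under the null hypothesis the interim and final statistics Z1 and Z2 are approximately bivariate normal with correlation √t. The overall error is

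1 − P(|Z1| < 1.96 and |Z2| < 1.96).

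| Information at interim, t | Correlation √t | Overall type I error |
| --- | --- | --- |
| 0.05 | 0.224 | 9.6% |
| 0.25 | 0.500 | 9.1% |
| 0.50 | 0.707 | 8.3% |
| 0.75 | 0.866 | 7.3% |
| 0.95 | 0.975 | 6.0% |

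The limits make sense: with unrelated looks the error would be 1 − 0.95² = 9.75%, and with identical looks 5%. In the same simulations, with the interim at 12 per group, rejection at either look occurred in 8.26% of runs (23 per group) and 8.33% (25 per group), which agrees with the 8.3% at t = 0.50.

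**Only the final test counts.** If the trial always continues and the interim result is never claimed, only |Z2| > 1.96 matters and the error is 5%, whatever the interim shows.

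**Thresholds that would hold the overall error.**

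- Haybittle-Peto, p < 0.001 at interim (|Z1| > 3.29) and 0.05 at the end: 5.06%, 5.02% and 5.00% overall for t = 0.25, 0.50 and 0.75.
- For comparison at t = 0.50, exactly 5% overall needs p < 0.0294 at both looks (Pocock), or p < 0.0052 at interim and p < 0.0480 at the end (O'Brien-Fleming).

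**Who sees what.** Section 8.2 means that individual allocations are known to the researchers in any case. What Section 10.4 adds is the aggregate between-arm comparison, given to the investigator. Section 11.2 puts the same role in contact with patients who have not yet consented. Section 9.5 names an independent body that could have received the comparison instead.

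**The case against.** The strongest reply is that Section 10.4 contains no efficacy stop and no early claim. If the trial simply continues, the final test keeps its 5%. That is correct, and it makes the inflation conditional. It would be tempting to read the section as setting the type I error at about 8%. The documents do not support that as a fact, because the decision rule is unstated and the information fraction is unknown.

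Three other inferences also go too far.

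- Section 12.6 says: "If the inclusion is not achieved within the stipulated time, we will make a report of the preliminary results". A reader might take this as a route for publishing the April 2018 result as the trial's outcome. It concerns a recruitment shortfall and does not mention the interim.
- A reader might suppose that interim knowledge affects how OMAS is scored. OMAS is a questionnaire that patients fill in, so the investigator has no direct route into that score. Range of motion and calf circumference are measured by research staff or doctors they train (Section 3), but nothing says that these people would see the interim result.
- The interim does not create the lack of blinding, which comes from the design. Nor does the protocol say that the investigator enrols patients; it shows only contact with recruitment.

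It can also be said that boundaries are often left to a statistical analysis plan, and that Section 10.4 does refer to DSMB advice. The first point would excuse silence. Here the protocol itself fixes the methods, and with them the 0.05 threshold. The second does not change who performs and sees the comparison.

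**Conclusion.** Wrong as written. The protocol commits the investigator to a between-arm interim analysis at an unadjusted 0.05 and keeps 0.05 for the final analysis, without saying what the look is for or what may follow from it.

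The size depends on that missing rule. If a significant interim result can be acted on or claimed, the two-sided error for one endpoint is about 8.3% with the look at half the information, and 9.1% to 7.3% for 25% to 75%. If only the final test counts, it is 5%. These figures assume two-sided testing and approximately normal test statistics. They cover repeated looks only; multiplicity across endpoints or OMAS time points is a separate matter and is not included.

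The disclosure of the emerging difference to someone in contact with recruitment does not depend on the decision rule. It arises even if the trial always runs to completion.

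**What to change.** Rewrite Section 10.4 in one of two ways.

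1. **Preferred.** Limit the April 2018 look to dislocations, serious adverse events, recruitment and data quality, reviewed by the DSMB named in Section 9.5, with no between-arm test of OMAS. State that the look has no efficacy purpose. The final test then keeps its full 0.05.
2. **If an efficacy look is kept.** State its purpose, the amount of data that triggers it and the decision rule. Use a Haybittle-Peto boundary (p < 0.001 at interim, 0.05 at the end; overall about 5.0%), and send comparative results to the DSMB only.

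The cost is one paragraph. Both options leave the final threshold at 0.05, so essentially no final power is lost. The investigator gives up an early look at efficacy. The change has to be made before the look takes place, because the comparison cannot be unseen afterwards.

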# ETHICAL CONSIDERATIONS

## Regulation statement

The study will be conducted according to the principles of the Declaration of Helsinki (64^th^ WMA General Assembly, October 2013) and in accordance with the Medical Research Involving Human Subjects Act (WMO).

## Recruitment and consent

All patients with ankle fractures at the emergency department of both locations of the Zuyderland Medical Center will receive information for participants on sight. The investigator informs the emergency doctors in advance to make a note in the patient files to confirm that the patients are informed about this study. Once a week the investigator will check if the patients got informed about the study. If not, the investigator will call the patients and he will send the participant information form by e-mail.

During their next visit after 7 to 10 days the patients are asked for their consent (see appendix).

